### Outcome measures

The schedule of enrolment and assessments that will be conducted in the study is shown in **Fig 3**.

**Fig 3 pone.0278428.g003:**
[figure not shown]
Schedule of enrolment and assessments for the FIFA football nurse protocol.

#### Primary outcome measure

*Current team medical practice*. Sports medicine practice will be evaluated at a cluster (team) level. This will be a self-administered questionnaire, which evaluates the teams’ current medical practice, their players and coaches’ sources of medical information, and their self-reported knowledge of injury management. It is adapted from previous work on medical practice in African sporting federations [11].

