## Materials and methods

### Football nurse intervention

The purpose of this study will be to evaluate the effect on teams’ sports medicine practice of randomising women’s football teams to a trained general nurse as a pitch side responder or usual practice. This study will be a cluster randomised control trial, whose reporting will follow the Consolidated Standards of Reporting Trials (CONSORT) 2010 statement: extension to cluster randomised trials [34]. Clusters will be registered teams in the Women’s Football League (24 teams) in Malawi. A 1x1 factorial design will be used to assess the effect of the FIFA Football Nurse intervention. The two allocated groups will be the football teams’ (clusters) sport medicine practice. The teams will be randomly assigned to intervention or control. Prior to the commencement of the intervention, a survey will be sent out to the women’s football teams to explore the current state of healthcare provision and policies for management or referral of players with injuries or illnesses, knowledge of injury prevention programs as well as their present medical needs. Following this, a cohort of 12 general nurses will receive a one (1) day training in basic football medicine using the latest version of the FIFA Emergency Care training manual. This training will be conducted by experienced sports medicine personnel as well as experienced trainers in basic life support (BLS) and first aid from the Departments of Emergency and Orthopaedics at Kamuzu University of Health Science (KUHeS), Blantyre, Malawi. Following the training, the nurses will be attached to a total of 12 women’s football teams during one competitive season. They will also be given access to reference materials that are adapted from the FIFA Emergency Care manual.

The roles of the nurses within the teams will include menstrual, basic health, injury risk assessment, nutritional, and mental health assessment; on field assessment, basic life support; immediate care, and referral of injuries; as well as maintaining records of injuries, illnesses, medication use and football exposure using standardised instruments as previously used in other studies [35, 36].

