#### Blinding

However, participants will not be aware of the entire ‘true’ purpose of the trial. They will be informed that they are being allocated a Football Nurse so that we can study the feasibility of this project in alleviating shortage of medical support in women’s football. Likewise, the INT group cannot be blinded as they will be aware of the Football Nurse assigned to them. However, the data will be coded and blinded before it can be analysed statistically.

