#### Standardisation of procedures

The physiotherapists and doctors will complete the modules from the freely and publicly available online FIFA Medical Diploma before the trial commences. This will allow for uniformity of football medicine practice and supervision among the participants during the trial. Shortly before the football season begins (1 week before), all the nurses and the physiotherapists/doctors will undergo a one (1) day training on emergency pitch side football medicine using the latest version of the FIFA Emergency Care training manuals. This training will be conducted by experienced sports medicine personnel ([name] and EC) as well as experienced trainers in basic life support (BLS) and first aid from the Departments of Emergency and Orthopaedics at KUHeS. Further, all research personnel will receive half a day’s training on the online data capturing system that will be used for the study. The research team will have access to written standard operating procedure on their mobile data collection devices as well. The team will also meet every fortnight to catch up and ensure adherence to standard research procedures.

The football nurse attached to each team will be primarily responsible for data collection for the INT teams and the research team, through a designated individual in the football team, will be responsible for data collection for the CON teams.

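### As written, collection of the sole primary questionnaire differs by arm, and in intervention teams it falls to the Football Nurse who delivers the intervention

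*Protocol article*

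**What the plan says.** Four sections of the protocol article bear on this.

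- **Primary outcome measure.** "Sports medicine practice will be evaluated at a cluster (team) level". The instrument is described as follows: "This will be a self-administered questionnaire, which evaluates the teams’ current medical practice". It also covers where players and coaches get medical information and "their self-reported knowledge of injury management". The section does not say who distributes or collects the form.
- **Standardisation of procedures.** "The football nurse attached to each team will be primarily responsible for data collection for the INT teams". For control teams the responsibility lies with the research team, working through a designated person in the team. The sentence is general and does not set the primary questionnaire apart.
- **Blinding.** "the INT group cannot be blinded as they will be aware of the Football Nurse assigned to them". Two partial safeguards are given: "participants will not be aware of the entire ‘true’ purpose of the trial", and "the data will be coded and blinded before it can be analysed statistically".
- **Football nurse intervention (Materials and methods).** Before the intervention starts, "a survey will be sent out to the women’s football teams to explore the current state of healthcare provision". That is a delivery route that does not involve the nurse.

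Team medical practice is assessed at the start, middle and end of the season (Secondary outcome measures).

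**The concern.** An unblinded self-report is open to courtesy and expectation effects in any trial. Here the route by which the answers are gathered also differs by arm. In intervention teams the general rule gives collection to the nurse who attends training and matches all season and whose assessment, immediate care and referral work is part of what team medical practice would be expected to cover. Respondents may answer practice and knowledge items more favourably when that person hands out or sees the form. In control teams the collector does not deliver the intervention under test.

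Such a shift would act in the direction of the stated hypothesis, that mean practice is higher in teams with a nurse. The primary comparison could not separate better practice from more favourable reporting. Coding the data before analysis acts after the answers have been given. The planned sensitivity adjustment for baseline practice does not remove a shift that arises after the baseline form.

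**Working it through.** **Inputs, all from Sample size:** SD 0.30, ICC k = 0.2, m = 25 per team, 12 teams per arm, target difference 0.19, two-sided 5% level, 80% power. The size of any reporting shift is not in the documents. The values 0.03, 0.05 and 0.10 are assumptions; they are 16%, 26% and 53% of 0.19.

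**The plan's own figure.** DEFF = 1 + 24 × 0.2 = 5.8.

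C = 1 + (1.96 + 0.84)² × (0.30² + 0.30²) × 5.8 / (25 × 0.19²) = 1 + 8.185 / 0.9025 = 10.07, which rounds up to 11 teams per arm. The stated 12 is one more, and is half of the 24 teams in the league. The difference is conservative and has no bearing on this point; 12 is used below.

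**Reading A: 0.30 is an individual-level SD.**

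- SD of a team mean = 0.30 × √(5.8/25) = 0.1445.
- SE of the arm difference = 0.1445 × √(2/12) = 0.0590.
- Critical t with 22 df = 2.074, so the smallest significant difference is 2.074 × 0.0590 = 0.122, or 64% of 0.19.

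**Reading B: 0.30 is the SD of team scores.** The outcome is said to be evaluated at team level, so this reading is possible.

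- SE = 0.30 × √(2/12) = 0.1225.
- Smallest significant difference = 2.074 × 0.1225 = 0.254.

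**Chance of p < 0.05 with no true effect** (two-sided t test on team scores, 22 df, non-centrality = shift / SE):

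| Assumed shift, intervention arm only | Reading A | Reading B |
|---|---|---|
| 0 | 5.0% | 5.0% |
| 0.03 | 7.8% | 5.6% |
| 0.05 | 12.8% | 6.8% |
| 0.10 | 36.8% | 12.2% |

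The table treats the shift as a net difference between arms. If control answers are also shaded upwards, only the excess in the intervention arm counts.

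**The case against.** The strongest objection is that no sentence says the nurse handles this particular form. The primary outcome section calls it self-administered and names no collector. The nurse's listed tasks are health, injury-risk, nutritional and mental health assessments, field care and referral, and records of injuries, illnesses, medication use and exposure; the team practice questionnaire is not among them. The control-arm description likewise covers only exposure and surveillance data. Read with these, the general sentence could be meant for surveillance and physical testing. The pre-trial survey goes to teams without the nurse, the schedule figure is not shown, and an article may leave distribution to operating procedures.

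This stands as a limit: the nurse's role with the form is an inference from a general rule. It does not remove the point, because that rule has no exception and, followed literally, gives the primary form different routes in the two arms.

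Three stronger readings are tempting, and the documents do not support them.

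- *The questionnaire rates the nurse.* It covers team practice, information sources and knowledge, so only part of it can reflect the nurse's work. Self-administered also means that the nurse does not fill it in for others.
- *Bias can arise in one arm alone.* Control teams report through an insider who may also shade answers. What is particular to the intervention arm is that the collector delivers the intervention.
- *The primary result is compromised.* The shifts are assumed, and their effect is much smaller if 0.30 is a team-level SD. Withholding the full purpose from participants may also soften expectation effects, although it does not hide the nurse.

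**Conclusion.** The point holds as a cheap improvement to how the primary outcome is collected. As written, collection differs by arm and in one arm is tied to the intervention provider, and neither coding before analysis nor baseline adjustment repairs a shift in the answers. For assumed net shifts of 0.03, 0.05 and 0.10 with no true effect, the false-positive chance rises from 5% to about 8%, 13% and 37% under the individual-level SD, or about 6%, 7% and 12% under the team-level SD. These figures show sensitivity to a shift. They do not estimate a bias that the documents let anyone measure. The conclusion rests on taking the general data-collection sentence to include the primary questionnaire.

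**What to change.** Amend Standardisation of procedures and Primary outcome measure to state that:

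- the existing research team sends the primary questionnaire directly to the same respondent roles in both arms at all three time points, as the pre-trial survey is sent out;
- it is completed under study codes and returned straight to the online data capture system;
- the Football Nurse neither distributes, collects, sees nor answers it.

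Name the respondent roles, since the primary outcome section does not fix them. Pre-specify a sensitivity analysis that repeats the primary comparison without the self-reported knowledge items.

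The cost is protocol wording, modest extra follow-up by the research team in the 12 intervention teams, and possibly slower returns there without the nurse's prompting. No observer or extra assessor is needed. The change removes the between-arm difference in collection. It leaves the open-label self-report bias, which should be stated as a limitation.

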#### Secondary outcome measures

*Demographic data and past medical history*. This will be a self- administered questionnaire on age, level of education, injury, and medical history. Additionally, players will complete a section on their menstrual history; namely, age at menarche, use of contraception, obstetric history, menstrual hygiene management practices, presence and management of menstrual cycle disorders as well as perceived effect of the menstrual cycle on football performance. This outcome will be evaluated at an individual participant level.

*Injury prevention and management behaviours*. A self-administered questionnaire will be used to evaluate injury prevention and management behaviours at an individual participant level as reported in other work [18, 40]. These will explore players’ and coaches’ knowledge, beliefs, and practices of injury prevention in football.

*Injury risk*. Individual intrinsic and extrinsic Injury risk will be assessed. Intrinsic injury risk will be assessed using functional movement screening (FMS^TM^), injury history, musculoskeletal assessment, and muscle endurance testing. The FMS consists of seven tests: overhead squat, single-leg hurdle, split squat, shoulder mobility, active straight leg raise, stability push-up and rotary stability. The musculoskeletal assessments will be; limb girths, ankle dorsiflexion (weight bearing lunge test), sit and reach, lumbar forward flexion, and lumbar spine extension. While muscle endurance testing will comprise prone elbow plank and bilateral side planks to exhaustion, and the number of push-ups and squats performed in 60 seconds. All these tests have been reported elsewhere [38] and can be performed with minimal equipment and were specifically chosen for their ease of administration by an individual even with minimal training. Extrinsic injury risk will include assessment of the team’s home training field players’ personal equipment and stadium health services as done by other researchers [11].

*Nutritional data*. Individual nutritional and dietary assessments will be performed using the 24-hour food recall questionnaires, which records one’s meals in the last 24 hours, the main sources of the food, timing of meals and the food portions [41].

*Mental health assessment*. This will be assessed using the Sports Mental Health Assessment Screening Tool-1 (SMART-1). The SMART-1 is a standardised assessment tool that aims to identify individual athletes potentially at risk for or already experiencing mental health symptoms and disorders to facilitate timely referral for those in need of support or treatment [42].

*Football exposure*: *Injury*, *illness*, *and medication use surveillance*. These data will be collected at a cluster level using injury, illness and football load forms as recommended in injury consensus statements [36]. The research team will follow up with each football nurse on a weekly basis to ensure surveillance data is being captured. Should an injury occur that requires investigations or further management, the nurses will refer to the PT/Dr, who will proceed with the treatment, design/prescribe further management and document accordingly. League performance will also be collated from FAM at the end of the season as this has previously been associated with injury rates in other team sports [43].

Assessment of injury behaviours, team medical practice, injury risk, nutritional data, and mental health assessment will be done at three time points: at the beginning before the trial begins, halfway through the trial, and at the end of the season. Football exposure and surveillance data will be collected and collated at the end of each training session and/or match until the end of the season.

*Measurement of potential confounders*. Despite all players playing in the same league and at the same level, primary confounders for injury risk include physical/ anthropometric characteristics; existing mental health or psychiatric conditions and home environment, which may influence the SMHAT- 1 values, for example. Secondary confounders include playing experience, playing position, and playing level as well as socio-economic status, which will affect nutrition, menstrual hygiene management and private management of injuries. Where possible, these will be considered in the analyses. Some of them will also be explored further in the qualitative interviews at closure of the protocol.

*Adherence*. This study has been designed to be optimally implemented in grassroots women’s football in a low-income setting. The researchers will monitor adherence of the nurses’ attendance at training sessions and matches using electronic record sheets. These records will then allow for exposure hours to be calculated and a measure of adherence to be determined. The surveillance data will be monitored on a biweekly basis to ensure it is up to date and following standardised operating procedures. The study is being performed in a league that has massive shortages of medical personnel and therefore, the participants in the intervention group will be motivated to adhere to the protocol as best they can.

*Ethical considerations*. Permission was sought and obtained from FAM and Directors of District and Social Services (DHSS) in all the regions where the women football teams are based. Ethical approval for this trial was obtained from the College of Medicine Research and Ethics Committee (COMREC), Blantyre, Malawi (protocol number: P.01/22/3551). The study will be conducted in accordance with the Declaration of Helsinki, the protocol and GCP guidelines. Before they can be a part of the study, and before randomisation, the investigators will explain the objectives of the study to the physiotherapists, doctors and nurses; football teams, their women players, and their coaching teams. They will only then be eligible to be included in the randomisation and eventual participation in the study after they have provided verbal and written assent and consent. This study will be voluntary, and participants will be informed that they have a right to participate or to withdraw from the study at any time, without prejudice. Data collected from the study will be stored in a password protected database and computer and that will only be accessible to the researchers. Study participants will be assured of their confidentiality. The names of the participants will only be on the consent form and in all other instances, they will be referred to by their assigned unique code.

In the event of a participant being flagged as being at risk of self-harm or harm to others in the mental health screening, the Football Nurses and their supervisors will be obliged to provide brief intervention within the scope of their practice, following which they will refer the participant for further management by the relevant healthcare providers. Should a medical condition be detected in the physical assessments, a similar approach will be taken in the management of the player.

*Data analysis*. Data will be analyzed using the IBM Statistical Package for Social Sciences (SPSS) version 21. The Shapiro-Wilk test for normality of the data will be conducted. Baseline comparability of participants for potential confounding factors such as age, length of football career, and baseline injury risk will be conducted using a chi-square test (for categorical variables) and either independent t-tests [normally distributed data] or Mann-Whitney U tests [non-normally distributed data] (for continuous variables).

Due to the relatively small number of clusters, data analyses will be based on summary level measures to account for the shortcomings of individual level regression methods. The primary variable of interest will be sports medicine practice. The mean (SD) sports medicine practice score will be calculated and presented by cluster and by arm. The mean of these mean scores and their associated 95% confidence intervals (CI) will then be presented for each arm. Linear regression of the mean sports medicine practice scores per cluster and per arm; two-way analysis of variance (ANOVA), will be used to explore the differences in sports medicine practice score and the 95% CI associated with the FIFA Football Nurse intervention by arm.

For the injury, illness, and medication use data, injury, illness, or medication use history will be recorded to determine the baseline injury, illness, or medication use risk. Injury, illness, and medication use rates and corresponding 95% CIs will be calculated for all players as the number of injuries/illnesses/medications reported per 1000 hours of football exposure (training and match). The severity of the injuries/illnesses, as scored by the number of days of missed training or matches, will also be calculated. Additional analysis will include, but not be limited to, the incidence and type of injury/illness/medication; chronic versus acute injuries/illnesses/medications; contact versus non-contact injuries and mechanism of injury (all per 1000 player hours). A Poisson regression will be used to compare differences in the injury, illness, or medication use rates between the control and intervention arms. To evaluate the impact of the FIFA Football nurse intervention on injury/illness/medication use outcomes, we will use logistic regression analysis to compare the proportion of players with injuries/illness/taking medications between the intervention and control arms, adjusting for potential confounding variables such as previous injury, age, playing experience, BMI, and playing conditions. We will also conduct subgroup analyses to determine whether the intervention has differential effects on different subgroups of players.

For the testing data such as injury risk (FMS, musculoskeletal screening), nutritional data (24h recall), and mental health assessment (SMHART-1), a mixed between-within-subjects ANOVA will compare the two arms over the whole intervention, then a post hoc Bonferroni test will be used to determine whether there are significant changes in the various scores and at what time point during the intervention these occur. Should there be a significant change in test scores, a one-way ANOVA will be performed at the specific time point to determine which specific test is different between arms. Additionally, a mixed effects logistic regression model will be used to examine the effects of arm assignment (intervention vs control) and time for categorical outcomes (e.g., sports injury prevention behaviours). To assess adherence and feasibility, descriptive statistics will be used to determine which aspects of the FIFA Football Nurse programme are best or worst implemented. Sensitivity analyses include adjustment for baseline team sports medicine practice and other potential confounding factors (e.g., previous injury, age, football experience, BMI, socioeconomic status). We will also include tests for effect-modification by relevant factors.

Additionally, data from the semi-structured interviews will be transcribed verbatim and a thematic analysis will be conducted using Braun and Clarke’s 6 step model [44] to group common themes and describe the experiences of women’s football stakeholders, and the barriers and facilitators towards the football nurse task-sharing approach. Analysis will be approached inductively by tagging meaning units which will then listed as themes, compared, and clustered to form categories, then assigned as general dimensions. Inter-rater reliability checks will be conducted by a blinded researcher, who will code a subset of the manuscripts and determine congruence of resulting themes. If clustering effects are observed in the data, these will be accounted for using appropriate statistical methods such as multilevel or hierarchical models.

All statistical tests conducted in this trial will be two-sided and p-values of < 0.05 will be considered statistically significant.

*Patient and public involvement*. Patients and the public were not involved in the design of this protocol. However, various stakeholders in Malawi women’s football (e.g., nurses, women football players, district sports officers, district representatives in women’s football) will be consulted on the conduct, reporting, and dissemination plans for the research.

*Project time frame*. This project will be performed over an 8-month period during the 2022/2023 football season (May to December).

May 2022 –training of nurses; recruitment of football teams; randomisation of teams.June 2022 –baseline testing of teams (assessment of injury behaviours, team medical practice, injury risk, nutritional data, and mental health assessment)June 2022 to December 2022 –implementation of the football nurse intervention; injury surveillance; adherence and exposure data collection.October 2022 –midway testing of teams (assessment of injury behaviours, team medical practice, injury risk, nutritional data, and mental health assessment)December 2022 –final testing of teams (assessment of injury behaviours, team medical practice, injury risk, nutritional data, and mental health assessment); semi-structured interviews with sample of players and coaches from both groups and all nurses

*Outcomes and significance*. We expect to develop a low cost, sustainable and context relevant solution to manage the treatment gap of football injuries/illnesses in underserved communities such as women’s football. Through the study, we also anticipate the development and maintenance of player health, injury and illness monitoring databases for Malawian women football players in club football, which can be replicated in grassroots women’s football leagues in LMICs. This will allow the monitoring of trends and development of relevant preventive or management strategies in these settings. Additionally, we expect this study to lead to the development of a flagship model which can inform implementation of similar task sharing approaches to SEM practice in other LMICs in Africa and globally.

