### Inclusion of nurses in task sharing in SEM

Perhaps, instead of having an SEM strategy that is heavily reliant on doctors and PTs as in HIC, we ought to adapt current global standards to fit the human resources profile of SSA and include the largest group of healthcare providers by numbers, nurses. In general medical practice, nurses currently conduct screening, diagnosis and management of medical conditions as well as referring to other healthcare workers as necessary and are an integral part of healthcare delivery in most LMICs [25, 30]. Similarly, they should be a key component to delivering health care services in football especially at grassroots levels and for underserved football players. Including nurses in the SEM practice agenda may help alleviate the shortage of pitch side medical care in women’s football teams. Additionally, as nurses are predominantly women [31], their inclusion into SEM practice will also help increase representation of African women SEM practitioners as they are still underrepresented in the profession [32].

Therefore, the aim of this project is to develop a task sharing approach (Football Nurse) to actively recruit and train nurses as pitch side responders in grassroots women’s football. Similar task sharing approaches have been used successfully in other sporting codes [33] and in LMICs to manage the diagnosis, treatment, and referral of other health conditions where there is a shortage of specialists [30]. The broad aim of this project is to explore the influence of trained nurses as pitch side responders in grassroots women’s football teams. Therefore, to minimise contamination, the unit of randomisation and analysis will be the football team.

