#### Control or standard care

In the control or standard care group (CON) consisting of 12 teams (clusters), each team will have 30 registered players, one (1) team manager, and one (1) coach and will continue their SEM practise ‘as per usual’. A member of the research team will contact a designated member of their technical personnel to collect data on football exposure; injury, illness and medication use surveillance after each training session and league match. Beyond this, the teams in the CON group will not receive any special instructions. It is noteworthy that the teams in the CON and INT groups will at some point in the season play against each other and the Football Nurse will be duty bound to render care should a player from the CON group be injured or fall ill during the match. Therefore, contamination cannot be entirely avoided.

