#### Sample size

The study aims to evaluate the impact of the Football nurse intervention on team sports medicine practice. Hence, the study will recruit twelve (12) nurses, with one assigned to each intervention team, and six (6) physiotherapists and/or doctors to supervise the Football Nurses from two teams each.

To determine the appropriate sample size, the study used the cluster randomized formula as in previous studies [38]. This formula considers the intra-cluster correlation coefficient, number of participants, expected effect size, and power of the study. The formula is as follows:

$$C=1+{\left(Z_{\alpha /2}+Z_{\beta }\right)}^{2}\frac{\left[\sigma_{0}^{2}+\sigma_{1}^{2}\right]\times [1+(m-1)k]}{m{\left(\mu_{0}-\mu_{1}\right)}^{2}}$$

Where C is the number of clusters required per treatment arm, *Z*_*α*/2_ and *Z*_*β*_ are the critical values of the standard normal distribution for the desired confidence level and power, respectively, *m* is the number of individuals per cluster and *k* is the intracluster coefficient, *μ*_1_ and *μ*_0_ are the true means, and σ_1_ and σ_0_ are the standard deviations, of the outcome variable in the presence and absence of the intervention, respectively.

The design effect of a CRT is related to the intracluster correlation coefficient as follows:

DEFF=1+(m−1)k

Assuming a 95% confidence level (*Z*_*α*/2_ = 1.96), a power of 80% (*Z*_*β*_ = 0.84), an expected effect size of 0.19 (based on a 50% increase in team sports medicine practice), a standard deviation of 0.30, an intra-cluster correlation coefficient of *k* = 0.2, and 25 participants per cluster, the study estimates that it will need 12 clusters (teams) in both the control and intervention groups. Therefore, a total of 600 participants will be recruited, with 300 participants in each group. In summary, the study will recruit twelve (12) nurses and six (6) physiotherapists/doctors to supervise the intervention teams. The study will need 12 clusters (teams) in both the control and intervention groups, with a total of 600 participants (300 in each group) to detect a statistically significant change in team sports medicine practice at a 95% confidence level and 80% power, using the cluster randomized formula [38, 39].

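### Baseline comparability is tested player by player although whole teams are allocated, so the p-values will be too small and will overstate imbalance between arms

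*Protocol article*

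**What the plan says.** All places are in the protocol article.

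- **Data analysis** (under Secondary outcome measures): "Baseline comparability of participants for potential confounding factors such as age, length of football career, and baseline injury risk will be conducted". Categorical factors get a chi-square test. Continuous ones get "either independent t-tests [normally distributed data] or Mann-Whitney U tests [non-normally distributed data] (for continuous variables"). No test has a cluster term.
- **Last sentence of Data analysis**: "All statistical tests conducted in this trial will be two-sided and p-values of < 0.05 will be considered statistically significant". This covers the baseline tests.
- **Inclusion of nurses in task sharing in SEM**: "the unit of randomisation and analysis will be the football team".
- **Trial design**: the 24 teams are drawn by name from three regional bowls into two arms of 12.
- **Sample size**: "an intra-cluster correlation coefficient of *k* = 0.2, and 25 participants per cluster", assumed for team sports medicine practice. The arm descriptions say that "each team will have 30 registered players".
- **Covariates**: the logistic model for injury, illness and medication use is described as "adjusting for potential confounding variables such as previous injury, age, playing experience, BMI, and playing conditions". The sensitivity analyses have a similar list. On measured confounders generally, the text says "Where possible, these will be considered in the analyses".

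**The concern.** The factors tested are characteristics of individual players, but players reach an arm only as part of a team. Team-mates are likely to resemble each other in age, playing history and injury background. The difference between arms therefore varies more from draw to draw than a player-level test allows for, and its p-value is too small. This conflicts with the article's own statement of the unit of analysis.

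A significance test of baseline also adds little under a random draw, because chance is already the known explanation for a difference that existed before allocation.

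What is at stake is the baseline comparison in the trial report. It could show several significant differences on factors that are as well balanced as a draw of 24 teams allows. Readers could then doubt a sound randomisation.

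**Working it through.** **Inputs.** Two-sided 5% level (Data analysis). 12 teams per arm, m = 25 participants per team, ICC k = 0.2 and design effect DEFF = 1 + (m − 1)k (Sample size). Alternative m = 30 (registered players per team). The ICCs of 0.01, 0.05 and 0.10 are assumptions, since the plan gives none for the baseline factors.

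**The plan's own figure.** The article states no error rate for the baseline tests, so there is none to reproduce. The same inputs in its sample-size formula give C = 1 + (1.96 + 0.84)² × (2 × 0.30²) × 5.8 / (25 × 0.19²) = 10.07, that is 11 teams per arm against 12 stated. That difference is on the safe side and does not bear on this point.

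**Rejection rate with no systematic difference between arms.** A player-level test uses a variance too small by the factor DEFF. Its nominal 5% cut-off then corresponds to a true rejection rate of 2 × [1 − Φ(1.96/√DEFF)].

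| Assumed ICC | DEFF (m = 25) | 1.96/√DEFF | Rate, m = 25 | Rate, m = 30 |
|---|---|---|---|---|
| 0 | 1.00 | 1.960 | 5.0% | 5.0% |
| 0.01 | 1.24 | 1.760 | 7.8% | 8.4% |
| 0.05 | 2.20 | 1.321 | 18.6% | 21.1% |
| 0.10 | 3.40 | 1.063 | 28.8% | 32.1% |
| 0.20 | 5.80 | 0.814 | 41.6% | 45.2% |

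**Check by simulation.** For 24 teams of 25 at ICC 0.2, the player-level t-test rejected in 42.1% of runs, Mann-Whitney in 40.6% and chi-square in 41.9%. A t-test on the 12 + 12 team means rejected in about 5%. Ignoring the team is therefore what causes the excess. For the t-test at ICC 0.05 and 0.10, simulation gave 18.6% and 28.8%.

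**Effect of the regional draw.** Drawing within region balances any team variance that is regional. If half of the between-team variance at ICC 0.2 were regional (an assumption), the simulated player-level rate would fall from about 42% to 29%.

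**The case against.** **The ICC of 0.2 belongs to another variable.** This stands. It was set for the sports medicine practice score. A reader might take 42% as the false-positive rate on the plan's own clustering, but the article gives no ICC for the baseline factors. The 42% is the top of an assumed range for m = 25. A reader might also combine the three named factors into a high chance of at least one false imbalance. That would need them to be independent, and age and length of career are plainly related.

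**Nothing in the analysis depends on these tests.** This largely stands. A reader might infer that baseline p-values will decide which confounders are adjusted for. The documents do not say so. The logistic model and the sensitivity analyses name their covariates without making them conditional on a baseline test. The 0.05 level applies to tests in general and is not a rule for admitting covariates. The lists differ and are open-ended, but an article may leave the final list to the analysis plan, so that is not counted here. The primary analysis compares team-level summaries.

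**A comparability check may have a purpose here.** The Project time frame puts randomisation in May and baseline testing in June. Nurses collect data in intervention teams, while control data come through a designated team member. A systematic difference in measured baseline is therefore possible, although consent is required before randomisation. This is fair, but a player-level test cannot tell such a difference from ordinary variation between teams.

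**The plan promises to handle clustering.** Data analysis says multilevel methods will be used where clustering shows up in the data. That promise is conditional, closes the paragraph on the interviews and does not name the baseline tests. The tests that are named make no allowance for clustering. The statement about summary-level measures comes after the baseline tests, and the detail that follows it concerns only the practice score.

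**Conclusion.** The point holds as a fault in a stated analysis. The planned baseline tests ignore the allocation of whole teams, contradict the stated unit of analysis and will overstate imbalance.

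The size rests on an ICC that the plan does not give. With 25 players per team, the true rate behind a nominal 5% test is about 8% at 0.01, 19% at 0.05, 29% at 0.10, and up to about 42% if 0.2 applied. It is lower where the regional draw balances part of the team variance. Each positive ICC tabulated gives a rate above 5%.

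The consequence is limited to a misleading baseline comparison that could wrongly suggest failed randomisation. The documents do not support going further: they neither select covariates on baseline p-values nor make the primary comparison depend on these tests.

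**What to change.** 1. Delete the baseline significance tests.
2. Describe baseline by arm without p-values: player-level mean and SD, or n and %, plus the spread of the 12 team means in each arm.
3. State that adjustment covariates are those named in advance for prognostic value, and that baseline p-values play no part in choosing them.
4. If a formal check is kept because baseline is measured after allocation, carry it out on team-level summaries.

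The cost is one paragraph of analysis wording. It needs no new data and less analysis than now planned.
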